## 3.6 Secondary Analyses

Secondary clinical outcomes that are Time to Event will be analysed in a similar way to the primary endpoint. The analyses will be performed on adjudicated events in the ITT population. Subjects who are alive and event free at the end of the trial will be censored at the date of trial completion. Subjects who die (for a non-mortality endpoint) or who die for a different cause than the endpoint under investigation will be censored at their date of death. Those lost to follow-up will be censored at the date that their status was last known.

The total number of unplanned hospitalisations (for cardiovascular reasons and for all reasons) will be analysed using the Andersen-Gill model, a Cox regression model for counting processes. We will also explore the use of Poisson regression (with duration of follow-up included as an offset) and negative binomial models, depending on the range of counts that are seen in the data.

Continuous endpoints will be analysed using Analysis of Covariance (ANCOVA) including the baseline value as a covariate where available. Variables that appear to be skewed following a visual inspection of the separate group histograms will undergo a two parameter Box-Cox transformation prior to analysis.

Analysis approaches for the Health Economics endpoints are discussed in the Health Economics section (Section 4).

All secondary endpoint comparisons will be performed using the ITT population, and will include the same covariates as the model for the primary analysis (site and device type) and will be conducted using a 5% significance level. All estimates will be presented with 95% confidence intervals. There will be no imputation of missing values or adjustment of the significance level for multiplicity.

Time to event comparisons will be visualised using Kaplan-Meier curves.

## 3.7 Extended Analyses

The regression models fitted for the primary and secondary analyses will be extended through the exploration of the influence of the other baseline variables on the outcome and through on-treatment analyses that track each participant’s actual remote monitoring status. The impact of different thresholds of remote monitoring adherence for the inclusion in the PP population will also be explored. In addition, sensitivity analyses will be performed on the secondary endpoints for the CV death ‘equivalent’ events - emergency heart transplantation, appropriate shock from ICD, LTAD insertion and survived resuscitation of sudden cardiac arrest.

### 3.7.1 Inclusion of additional covariates

The primary and secondary analyses will be repeated, additionally including gender and baseline NYHA classification as fixed effect categorical variables and age at randomisation as a continuous covariate.

An additional set of exploratory analyses will examine the impact of further covariates from the baseline visit. For each of the primary and secondary analyses the impact of the following variables will be explored:

1. Diabetes:
   1. Type (none, type 1 or type 2).
   2. Treatment (insulin dependent or not).
2. Aetiology (Ischaemic or non-ischaemic heart failure).
3. Medication use (including beta-blockers, ACE/ARB, MRA, diuretics).
4. Body mass index (BMI).
5. Systolic blood pressure.
6. Pulse pressure.
7. LVEF.
8. Haemoglobin.

### 3.7.2 Proportion of remote monitoring for inclusion in per protocol Analysis

The threshold used for including participants in the PP analysis set, based on their percentage of remote monitoring that was conducted, will be explored. A range of different threshold percentages for successful monitoring will be used, with the impact on the treatment effect examined. This will enable us to explore whether the completeness of the monitoring has any impact on its effectiveness.

### 3.7.3 On-treatment (on-monitoring) analyses

The term on-treatment in this trial refers to the participants being actively, remotely monitored. Time periods where the actual remote monitoring status of the participants changes over time (for any given individual) will be analysed according to the actual status of the remote monitoring. In effect a patient who changes remote monitoring status will switch between the two treatment groups. This is achieved by the introduction of time-dependent treatment indicator variables. However, the fact that trial participants are switching between groups means that on-treatment analyses are no longer protected from bias by the randomisation process, and hence we fully acknowledge that they should be interpreted with caution.

## 3.8 Subgroup Analyses

The following subgroups have been defined prior to the randomisation code break:

- Age (<70 years, ≥70 years).
- Gender.
- NYHA (≤II vs. >II).
- Type of device (ICD, CRT-P and CRT-D)
- Ischaemic / non-ischaemic heart failure.
- Occurrence of shock therapy.

Target outcomes (the primary endpoint and selected secondary endpoints) will be presented by the given subgroups and compared using interaction tests. To facilitate this testing, an interaction term between the treatment comparison and the subgroup variable will be added to the relevant model for each of these subgroup analyses.

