**6 Inclusion and Exclusion Criteria**

***Inclusion Criteria:*** Devices will be either Implantable Cardioverter Defibrillators (ICDs) or Cardiac Resynchronisation Therapy-Defibrillators (CRT-Ds) or Cardiac Resynchronisation Therapy-Pacemakers (CRT-Ps) (as the required monitoring features are currently available only in those device types). Participants will all have received an ICD, CRT-P or CRT-D at least six months previously, for the treatment and monitoring of chronic heart failure. Patients receiving these devices will be doing so according to NICE guidance and/or local clinical discretion and not for the purposes of this study. In addition patients should meet all of the following criteria:1) Be on stable medical therapy for CHF for 6 weeks prior to recruitment; 2) Will have the ability to independently comprehend and complete Quality of Life Questionnaires; 3) Will have the ability to give informed consent; 4) Will be on optimal medical therapy according to the treating physician, working to NICE Guidelines; 5) Will have had their device programmed to give optimal therapy according to the treating physician; 6) Will have symptomatic heart failure (i.e. NYHA Class II to IV) documented at the time of study enrolment.; 7) Will be at least 30 days post any device change or lead replacement procedure; 8) Will be at least 3 months post any cardiac surgical procedure; 9) Will be at least 3 months post acute myocardial infarction.

***Exclusion Criteria:*** Participants will be excluded from the study if they meet any of the following criteria: 1) Unable to use the technology due to mental or physical limitations 2) Less than 18 years old 3) Pregnancy 4) On a heart transplant list 5) Life expectancy of < one year (non cardiovascular related) in the opinion of the treating physician 6) Current device related complications, e.g. wound infection or haematoma, lead fracture, 7) Device implanted less than 6 months previously. 8) Patients unable to understand written and spoken English.

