***Statistical analysis:***

Cox proportional hazards regression will be used to analyse the primary outcome data according to the intention to treat. The stratifying variables will be entered as covariates and any clinically important baseline imbalance will also be accommodated in the model. Estimates will be reported as hazard ratios with 95% confidence intervals. Secondary clinical outcomes with time to event will be analysed in a similar way using a multifactorial survival analysis modelling method appropriate to the multicentre nature of the data (i.e. to allow for centre effects).

We will censor at time at study end for those alive and free of hospitalisation and at last date known to be free of hospitalisation for those who are lost to follow-up (e.g. leave the area). Withdrawals from RM will be recorded but such will be analysed at ITT.

Quality of life outcomes will be analysed at 1 and at 2 years.

From Euroqol : utility, VAS.

From SF12: Utility; Mental component score (MCS); Physical component score (PCS)

Kansas Heart failure numerical score.

Results will be analysed by multiple or logistic (if pre-specified categories) regression. Multiple imputation will be used to explore the impact of missing data in QoL data.

Cumulative number of unplanned CV hospitalisations will be analysed by multinomial logistic regression

A priori sub group analysis for the primary outcome will be conducted on the following variables:

Age

History of atrial fibrillation

Type of device (ICD, CRT-P,CRT –D)

Baseline functional status (NYHA grade, Kansas HF score).

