## 2.3 Study Power and Sample Size

Our sample size calculation is driven by a required number of events and uses event rate estimates from previous studies: this is an event-driven trial. The UCP group event rate is estimated from the COMPANION^2^ and CARE-HF^3^ trials, that both had a patient population that we expect to be comparable to our study control group. These trials reported 48% for any death or CV disease hospitalisation at 2 years, and 39% at 29 months for CV death or unplanned hospitalisation, respectively. We anticipate slightly lower rates in this trial due to an improvement in routine care, and so assume a 40% event rate for our primary endpoint of all-cause mortality or unplanned CV hospitalisation (see 3.2.1) in the control arm at 2 years.

The meta-analysis of Clark et al^4^ that looked at telemonitoring or structured telephone support, reported a 20% risk reduction compared to usual care. Hence we assume that the intervention group will have an event rate of 32% at two years. This reduction in event rate (from 40% to 32%) at two years, if seen, would be clinically relevant.

Fixing a 5% (2-sided) significance level and 90% power, 546 events are needed to detect this effect size in a log-rank survival comparison of the two trial groups. To achieve this number of events we are likely to require 1394 patients in total (697 per group) with a minimum follow-up of 2 years. We will inflate this total by approximately 20% to allow for attrition, giving a final recruitment figure of 1650. This sample size would also be sufficient to provide a reasonable estimate of the effect size in the individual components of the primary outcome – ACM and CV disease related unplanned hospitalisation. This sample size is considered feasible within the trial timescales.

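### SAP 3.8 tests the age interaction on a cut at 70 rather than on age in years, and leaves out the protocol's Kansas score and atrial fibrillation subgroups without explanation

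*Combined protocol and SAP*

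**What the plan says.** The protocol (section 10, Statistical analysis) commits to the following: "A priori sub group analysis for the primary outcome will be conducted on the following variables". Its list is age, history of atrial fibrillation, type of device, and "Baseline functional status (NYHA grade, Kansas HF score". It gives age no functional form.

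SAP 3.8 lists "Age (<70 years, ≥70 years" and "NYHA (≤II vs. >II", together with gender, device type, ischaemic aetiology and shock therapy. The test is described thus: "an interaction term between the treatment comparison and the subgroup variable will be added to the relevant model". The tested variable is therefore the cut one. Neither the Kansas score nor atrial fibrillation appears in 3.8.

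Elsewhere, SAP 3.7.1 adds "age at randomisation as a continuous covariate", but only as a main effect in the extended models. No continuous treatment-by-age term is planned anywhere. SAP 4.4.3 still describes atrial fibrillation as a defined subgroup when it sets out the drug costing. The Kansas questionnaire is completed at enrolment (protocol section 9; SAP 2.4.1), and SAP Table 4c tabulates its baseline scores. I take the protocol's Kansas questionnaire and the SAP's KCCQ to be the same instrument.

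**The concern.** There are two separate matters.

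The first is efficiency. The trial is sized for the overall comparison, and no power is stated for any interaction. Interaction tests are weak in such a design, and reducing age to two groups makes this one weaker. A real gradient of benefit with age would more often be reported as no evidence of interaction.

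The second is consistency. The SAP sets out to specify the protocol's methods further, yet two of the protocol's a priori subgroup variables have gone and no reason is recorded. With the Kansas score missing, functional status is examined only through NYHA. Eligibility requires this: "Will have symptomatic heart failure (i.e. NYHA Class II to IV) documented at the time of study enrolment". The split is therefore in effect class II against III/IV, and the finer measure that the trial already collects is unused.

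**Working it through.** **Inputs from the documents.** 546 events, 5% two-sided, 90% power, and 40% against 32% at two years (SAP 2.3); 1:1 allocation (SAP 1.2.2).

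**Assumptions.** Age is normal, and the log hazard ratio changes linearly with age. The trial's age rows are empty table shells. The only age figure is a mean of 72, without an SD, in the external cost cohort of protocol Appendix I. I therefore show ranges for the mean and SD.

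**1. The plan's own figure.** The plan states: "Fixing a 5% (2-sided) significance level and 90% power, 546 events are needed to detect this effect size". Under proportional hazards, HR = ln(0.68)/ln(0.60) = 0.755.
- Schoenfeld: 4 × (1.960 + 1.282)² / (ln 0.755)² gives 533 events.
- Freedman: (1.960 + 1.282)² × [(1 + 0.755)/(1 − 0.755)]² gives 540 events.

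Both are within 3% of 546, so the event count reproduces. It concerns the main effect only.

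**2. Information lost by one cut.** For a cut at c SDs from the mean, the share of information kept is φ(c)² / [Φ(c)(1 − Φ(c))]. At c = 0 this is 2/π = 0.637, a loss of 36.3%.

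| Mean age | Loss, SD 8 to 13 |
|---|---|
| 70 | 36.3% |
| 68 or 72 | 37.8% to 36.9% |
| 66 or 74 | 41.9% to 38.5% |
| 64 or 76 | 48.3% to 41.1% |

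**3. Power at 546 events, cut at the mean.** With slope b per SD of age:
- Continuous test: z = b / √(4/546).
- Cut test: z = 1.596b / √(4/273 + 4/273), where 1.596 SD is the gap in mean age between the halves.

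| b | HR ratio between halves, exp(1.596b) | Power, cut | Power, continuous |
|---|---|---|---|
| 0.10 | 1.17 | 15% | 22% |
| 0.15 | 1.27 | 29% | 42% |
| 0.20 | 1.38 | 46% | 65% |
| 0.25 | 1.49 | 64% | 83% |
| 0.30 | 1.61 | 80% | 94% |

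Indexed by the power of the continuous test, a central cut takes 50% to 35%, 70% to 51%, 80% to 61% and 90% to 73%. The largest drop is 19.4 points at a 36.3% loss of information, 19.8 at 37% and 23 at 42%.

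**4. Simulation check.** I fitted Cox models to simulated trials (mean age 70, SD 10, about 560 events, 600 runs per setting). Power, continuous against cut, was 67% vs 50%, 80% vs 58% and 90% vs 69%. The drops are 17 to 22 points, with simulation error of about 2 points on each power.

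**5. The opposite case.** Suppose the effect is a step at 70, with a log HR ratio of 0.4 and the cut at the median. The cut gives z = 0.4 / √(4/273 + 4/273) = 2.34, power 65%. The linear term keeps 0.637 of that information: z = 2.34 × √0.637 = 1.86, power 46%.

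**6. NYHA.** The class mix is not given. With linear scores, splitting II from III/IV loses 4% for an assumed mix of 70/29/1 (% in classes II/III/IV), 13% for 60/35/5 and 18% for 50/40/10.

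**The case against.** The best defence is that a two-group cut is an ordinary way to carry out a subgroup analysis by age. It was fixed before the code break, it matches the categorical subgroup tables planned in SAP 6.1.2, and it suits a reader who wants an estimate per group. Using age as a continuous main effect in 3.7.1 does not settle the form of an interaction. Steps 3 and 5 also mirror each other: whichever shape is true, the mismatched test has 46% power against 65%. The documents offer no evidence on shape. All of this stands, and it is why the point is a suggestion about efficiency.

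A reader might infer more than the documents support:
- **That the age cut contradicts the protocol.** It does not, because the protocol never says age would be continuous.
- **That 37% and 19 points are established, or that 19 is a ceiling.** They depend on an assumed age distribution and a linear gradient. An off-centre cut loses more.
- **That the NYHA split costs as much as the age cut.** Nothing shows this. Under the assumed mixes the loss is smaller.
- **That subgroup results will decide who is offered monitoring.** The documents do not say so.

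The defence does not reach the missing Kansas score and atrial fibrillation. No reason is given for either omission, and SAP 4.4.3 is at odds with 3.8 on atrial fibrillation.

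**Conclusion.** The point holds as a cheap improvement. The age interaction test uses less information than the trial holds. The loss is about 36-38% if age is roughly normal with a mean within about two years of 70 and any gradient is linear, and it rises towards 48% if the mean lies six years away. In power terms this is roughly 15-20 points for a central cut, over the range where the continuous test would have 50-90%. The cost of the NYHA split is not established.

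The firmer finding is textual: the Kansas score and history of atrial fibrillation are on the protocol's a priori list and absent from SAP 3.8, unexplained. The primary analysis is unaffected.

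**What to change.** In SAP 3.8:
- Base the age interaction p value on treatment by age in years, linear, with a prespecified spline as a check on shape.
- Restore treatment by baseline KCCQ overall summary score, continuous. Name that score, because SAP Table 4c lists several.
- Restore treatment by history of atrial fibrillation, which also brings 3.8 into line with 4.4.3.
- Keep age under/over 70 and the NYHA split as display categories with their estimates.

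If either protocol variable is left out on purpose, state the reason.

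The cost is a few changed or added model terms on data already collected. There are two downsides: lower power than the cut if the effect jumps at exactly 70 (46% vs 65% in step 5), and two more exploratory interaction tests in a section that mentions no multiplicity adjustment. The category estimates remain on display for the first. The second is met by labelling the tests exploratory.

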**5) Ventricular Arrhythmias**

Summary chart:

**
[figure not shown]
**

This chart summarises the approach to ventricular arrhythmias.

Your key role in management of ventricular arrhythmias is to identify their occurrence and change in burden. Both may indicate the need for a change in heart failure therapy, antiarrhythmia drug therapy, device programming (both for detection and therapy) and sometimes a further intervention such as ablation or device revision.

In the main you should discuss all these issues both with the technologist staff and the responsible physician. You should not initiate any therapeutic change without discussion with the responsible cardiologist.

However, you should be sufficiently acquainted with these issues to understand when it is appropriate to initiate a discussion about device therapy.

Do not forget to ensure that there are no changes that have taken place in patient medication or status that may have impacted on susceptibility to arrhythmia. Thus ask for primary care review of renal/electrolyte status and consider other co-morbidities or drug changes. Specifically ask patients questions to evaluate this. We are particularly keen to understand why change is occurring in arrhythmia stability status.

The two main arrhythmias to consider are management of monomorphic and polymorphic ventricular tachycardia as listed above.

Monomorphic ventricular tachycardia, even at fast rates, is often amenable to antitachycardia pacing. The precise programming of this can vary greatly and firm guidelines are difficult due to he breadth of the evidence base and its variability. It is necessary to ensure that all possible is done to avoid delivery of shock therapy when ATP my have been successful and this is the principle that will be adopted by technology staff and physicians. The concept of shock reduction will be specifically addressed during the training period and may be updated over the course of the study.

Antiarrhythmic drugs are useful adjuncts. In patients with a high burden of arrhythmia or with slow VT that is resistant to pace-termination and/or very frequent then catheter ablation may be an excellent therapy.

Polymorphic ventricular tachycardia is likely to be mush less amenable to ablation intervention but care should be taken to evaluate all the other issues mentioned above and in particular change in ischemia status or renal/electrolyte status.

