### 4.4.3 Medication Costs

The REM medication questionnaire collected data on 11 classes of CVD related drugs, by name. Mean cost per day for each of the more commonly used drugs will be estimated, with class means used for those used rarely or lacking full data. The prices will be combined with recommended daily dose to provide a medications cost per patient in each arm.

Clinical opinion suggests that efficacy was most likely to apply to changed use of diuretics. Aldosterone antagonists also matter due to their potential effect on mortality. The levels of use of each of these classes of drug will be shown separately. As AF was defined as a subgroup for analysis, the relevant drugs (warfarin, NOACs) will also be identified and costed separately. Cost units for all drugs will be calculated based on BNF.

System modifications (to the implanted device) would normally require an outpatient or day-case attendance. These will be identified by attendance type and costed as standard attendances.

Serious adverse events (SAEs) requiring hospitalisation are identified in the SAE questionnaire. The number of hospital days in each arm for SAEs and any other relevant conditions will be multiplied by mean NHS national HRG cost. This will be expressed as cost per day by dividing by mean length of stay^6-7^.

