### 6.1.2 Planned Outcome tables

Table 5: Hazard ratios for Primary and Secondary Time to Event Endpoints (ITT population).

Table 6: Relative risks for number of hospitalisations (ITT population).

Table 7a: Change in QoL scores from baseline to 2 years (ITT population).

Table 7b: Change in QoL scores from baseline to 1 year (ITT population).

Table 8: Health Economics Outcomes.

Tables 9 to 63: Replicates of Tables 5, 6, 7a, 7b and 8 in each of the 11 pre-specified subgroups (ITT population).

Tables 64 to 68: Replicates of Tables 5, 6, 7a, 7b and 8 (PP population). – Including Multiple Imputation results where applicable.

Table 69: Treatment related serious adverse events (ITT Population).

Table 70: Serious adverse reactions not considered related to treatment (ITT Population).

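### SAP 3.8 uses shock therapy as a subgroup without saying when the shock occurs, and omits two of the protocol's a priori subgroups (AF history and Kansas HF score)

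*Combined protocol and SAP*

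**What the plan says.** SAP 3.8 introduces its list with "The following subgroups have been defined prior to the randomisation code break". The list is age, gender, NYHA class, device type, ischaemic aetiology and "Occurrence of shock therapy". Each is tested by the same method: "an interaction term between the treatment comparison and the subgroup variable will be added".

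The a priori list in protocol section 10 (Statistical analysis) is different. It has age, "History of atrial fibrillation", device type, and baseline functional status by NYHA grade and Kansas HF score. Shock is not on it.

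SAP 4.4.3 says: "As AF was defined as a subgroup for analysis, the relevant drugs (warfarin, NOACs) will also be identified and costed separately". SAP 6.1.2 plans Tables 9 to 63 as replicates of five outcome tables "in each of the 11 pre-specified subgroups".

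Shocks appear in three other places:
- The remote monitoring handbook (protocol Appendix II, section 5) wants to ensure that "all possible is done to avoid delivery of shock therapy when ATP my have been successful".
- The ERC charter (SAP 7.1) classes an unplanned admission for an ICD shock as a cardiovascular hospitalisation.
- SAP 3.7 names as death equivalents "emergency heart transplantation, appropriate shock from ICD, LTAD insertion and survived resuscitation of sudden cardiac arrest".

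**The concern.** A subgroup analysis keeps the protection of randomisation only if the subgroup is fixed before treatment starts. If patients are sorted by whether they were shocked during the trial, and one arm's care aims to prevent shocks, the shocked and unshocked patients in the two arms are no longer alike. High-risk patients spared a shock in the remote-care arm move into that arm's no-shock group and raise its event rate.

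The subgroup also overlaps the outcome, because an admission for a shock can be the primary event. SAP 3.7.3 gives this kind of warning for the on-treatment analyses; 3.8 gives none.

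Separately, a subgroup named in advance in the protocol has disappeared from 3.8 while another SAP section relies on it. If this is left open at code break, the choice of subgroups can look driven by the data.

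**Working it through.** **1. The plan's own count.** Tables 9 to 63 are 63 − 9 + 1 = 55 tables, and 55 / 5 = 11 subgroups, as 6.1.2 states.

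**2. The lists side by side** (shock taken as yes/no):

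| Factor | Protocol 10 | SAP 3.8 | Levels in 3.8 | Planned baseline table |
|---|---|---|---|---|
| Age | yes | yes | 2 | Table 1 |
| Gender | no | yes | 2 | Table 1 |
| NYHA | yes | yes | 2 | Table 1 |
| Device type | yes | yes | 3 | Table 1 |
| Ischaemic aetiology | no | yes | 2 | Table 1 |
| Shock therapy | no | yes | 2 | none |
| AF | yes | no | – | Table 1 |
| Kansas HF score | yes | no | – | Table 4c (KCCQ) |

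SAP 3.8 gives 2+2+2+3+2+2 = 13 levels, not 11. Leaving out shock gives 11. The protocol's list also gives 11 if age, AF, NYHA and Kansas score are each split in two (2+2+3+2+2). The count therefore shows that 6.1.2 does not match 3.8, but not which list the tables were built for.

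**3. Timing.** Shock is the only one of the six factors in 3.8 without a baseline row. Elsewhere it is a follow-up event. Appendix II also aims to avoid shocks through rate control (section 4, rapid AF) and through re-programming (section 6).

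**4. Arithmetic illustration** (assumed inputs, deliberately extreme, no treatment effect on outcome). Suppose 20% of patients are high-risk with 70% events and 80% are low-risk with 32.5%, so 0.20×0.70 + 0.80×0.325 = 40% overall. Every high-risk usual-care patient is shocked; remote care averts half of those shocks.
- No-shock stratum, usual care: 32.5%.
- No-shock stratum, remote care: (0.10×0.70 + 0.80×0.325)/0.90 = 0.33/0.90 = 36.7%.
- Risk ratio without shock: 36.7/32.5 = 1.13. With shock: 70/70 = 1.0.

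With 825 per arm, the variance of the log ratio of risk ratios is 0.633/272.3 + 0.675/214.5 + 0.3/57.75 + 0.3/115.5 = 0.0133, so the SE is 0.115. Then z = ln(1.128)/0.115 = 1.05, and the interaction test would reject at 5% about 18% of the time.

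**5. Simulation.** A Cox model with a treatment-by-shock interaction and a shared gamma frailty linking shock risk to event risk. The documents give none of these inputs, so they are assumed: shocks at 8% to 15% a year, frailty variance 0 to 2, and 0 to 70% of shocks leading to cardiovascular admission.

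| Assumption | Overall HR | No-shock HR |
|---|---|---|
| No direct effect, shocks unchanged | about 1.00 | about 1.00 |
| No direct effect, shocks halved | 0.91 to 1.01 | 0.98 to 1.10 |
| One such case (variance 2, 15% a year, 70% admitted) | 0.944 | 1.094 |

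With shocks halved, the gap between the two hazard ratios ran from 0.014 (1.006 against 1.020) to 0.150 (0.944 against 1.094). A shock variable fixed before randomisation gave stratum hazard ratios equal to the overall one within simulation error.

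Overlap with the endpoint matters even if remote care leaves shocks unchanged. With a true HR of 0.755 on other events, 70% of shocks leading to admission and no frailty, the strata gave 0.755 (no shock) and 0.916 (shock), a ratio of 1.21.

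At trial size (1650 patients, 8% shocks a year, up to 30% leading to admission), the interaction test on follow-up shocks rejected in 3% to 5% of runs. Higher admission shares were not run at that size.

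**The case against.** Several stronger readings are tempting, and the documents do not support them.

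- **The subgroup can only mean shocks during the trial.** Section 3.8 gives no timing. Protocol section 6 requires a device in place for at least six months, so a prior shock history could exist. SAP section 6 lets table content change, so a missing row is not proof. What is certain is that timing is undefined; follow-up shocks are the likelier reading.
- **Remote care changes the shock rate.** The documents state an aim, not a result. Monitors may not change ventricular arrhythmia therapy without the cardiologist, all participants enter with optimally programmed devices, and usual device care continues. This weakens the presumption of a large difference between arms. It does not make the variable a baseline one. Appendix II also notes that shocks may be asymptomatic or nocturnal, so weekly downloads might detect more of them in one arm; that is an inference.
- **The interaction test will be falsely significant.** The trial-size runs stayed near nominal, and even the extreme illustration gives about 18%. A large excess is not shown.
- **Counting appropriate shocks as death equivalents would hide a programming effect as fewer deaths.** This applies only to sensitivity analyses of secondary endpoints, and the Table 5 footnote reports ACM and CV mortality with and without the equivalents. Whether to keep shock there is a matter of preference.
- **AF is the subgroup with the clearest mechanism and will go unanalysed.** SAP 4.4.3 expects efficacy mainly through diuretic changes, and a history-of-AF subgroup does not isolate newly detected AF. Section 4.4.3 still treats AF as a subgroup, so the fault is a contradiction and an unexplained omission.

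**Conclusion.** The point holds as a should-fix. The shock subgroup is undefined and, on its likelier reading, conditions on a variable that arises after randomisation, that one arm aims to alter, and that overlaps the primary endpoint. The harm is that the stratum hazard ratios cannot be read as subgroup effects. The size of the distortion rests on assumed shock rates, risk clustering and admission shares, and it is close to nil if remote care has neither a direct effect on outcome nor an effect on shocks.

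The omission of AF history and Kansas HF score, the conflict between 3.8 and 4.4.3, and the mismatch of 13 levels with 11 subgroups follow from the text (the 13 takes shock as yes/no). The primary analysis is untouched.

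**What to change.** Before code break:

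1. In SAP 3.8, delete the shock subgroup. Only if shock history before randomisation was recorded, redefine it as that history in ICD and CRT-D patients. Label any analysis of shocks during follow-up as exploratory and non-randomised.
2. Reinstate history of AF as yes/no at baseline.
3. Reinstate Kansas HF score with a stated cut-point, or give the reason for removing it.
4. Make 3.8, 4.4.3 and 6.1.2 agree. Deleting shock and adding AF gives 11 + 2 = 13 levels and 13×5 = 65 tables (9 to 73). Adding Kansas score in two bands gives 15 levels and 75 tables (9 to 83). Later tables need renumbering.

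The cost is mainly SAP wording and table shells, since AF and KCCQ are already in the baseline tables. Swapping shock for AF keeps six interaction tests per outcome; Kansas score makes seven. If the tests were independent and unadjusted, the chance of at least one false positive would go from 1 − 0.95^6 = 26% to 1 − 0.95^7 = 30%, so these results should stay supportive. The baseline redefinition of shock may not be possible if the history was never collected; deletion is then the only clean option.
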